# Efficacy of a plant-based diet on FOLFOX chemotherapy-induced gastrointestinal toxicity in patients with colorectal cancer: study protocol for a multicentre, stratified, randomised controlled trial

**DOI:** 10.1186/s13063-026-09573-y

**Published:** 2026-03-03

**Keywords:** Colorectal cancer, Chemotherapy-induced gastrointestinal toxicity, CIGT, FOLFOX, Plant-based diet, Inflammation, Gut microbiota, Metabolomics

## Abstract

**Background:**

Gastrointestinal toxicity during FOLFOX chemotherapy for colorectal cancer (CRC) is frequent and can impair oral intake, quality of life, and planned chemotherapy delivery. Safe and scalable dietary strategies are needed as adjuncts to standard supportive care. This trial will evaluate whether a structured plant-based dietary strategy reduces chemotherapy-induced gastrointestinal toxicity (CIGT) and improves related biological and patient-centered outcomes.

**Methods:**

This multicentre, stratified, three-arm, parallel-group, assessor-blinded, superiority randomised controlled trial will enrol 114 adults (18–65 years) with pathologically confirmed CRC receiving (or scheduled to receive) FOLFOX chemotherapy at two hospitals in Chengdu, China. Participants will be randomised (1:1:1), stratified by study site and sex, to (1) a structured plant-based dietary strategy, (2) conventional dietary guidance, or (3) conventional dietary guidance plus an oncology complete nutritional formula, for 6 weeks. Assessments will be performed at baseline and at prespecified time points through week 6. Primary outcomes are (i) the participant-level incidence of any prespecified CTCAE gastrointestinal toxicity of grade ≥ 2 during follow-up, (ii) serum inflammatory biomarkers, and (iii) stool-based profiling. Secondary outcomes include dietary intake and diet quality, body composition by bioelectrical impedance analysis, routine clinical laboratory indices, fatigue, anxiety/depression, physical activity, and adverse events. Primary analyses will follow the intention-to-treat principle.

**Discussion:**

This trial will provide evidence on the efficacy and safety of a plant-based dietary strategy to mitigate CIGT during FOLFOX chemotherapy. Integrated clinical, biomarker, and stool multi-omics measures may also support exploration of biological correlates of symptom burden and treatment tolerance.

**Trial registration:**

Chinese Clinical Trial Registry (ChiCTR), ChiCTR2500095215; registered 03 January 2025. https://www.chictr.org.cn/showproj.html?proj=254099.

**Supplementary Information:**

The online version contains supplementary material available at 10.1186/s13063-026-09573-y.

## Protocol version {2}

Protocol version 3.0, Dated 16 January 2026.

## Introduction

### Background and rationale {9a}

Colorectal cancer (CRC) remains a major global health burden, with approximately 1.92 million new cases worldwide in 2022, and China accounting for nearly one-third of the global burden as incidence continues to rise [1, 2]. Systemic chemotherapy is central to the management of CRC, with FOLFOX (oxaliplatin, leucovorin, and 5-fluorouracil) being widely used as a first-line regimen for advanced disease [3]. It can exert direct cytotoxic effects on tumour cells, thereby delaying disease progression and prolonging survival in patients with CRC [3, 4]. However, chemotherapy is frequently accompanied by a spectrum of treatment-related toxicities, including myelosuppression, neurotoxicity, hypersensitivity reactions, fatigue, and chemotherapy-induced gastrointestinal toxicity (CIGT) [5]. Among these, CIGT is one of the most common and clinically consequential toxicities, typically manifesting as nausea, vomiting, anorexia, mucositis, and diarrhoea [6]. These CIGT symptoms can substantially reduce patients’ quality of life, compromise chemotherapy delivery through dose reductions, delays, or discontinuation, and increase healthcare utilisation and supportive medication costs, thereby adding to patients’ financial burden [6, 7].

At present, the management of CIGT relies mainly on pharmacological prophylaxis and symptom-directed supportive care [8]. Although pharmacotherapy can relieve associated symptoms, its high costs and potential adverse effects may limit long-term use and broad implementation in routine clinical practice [9]. This highlights a clear need for safe, patient-acceptable, and scalable non-pharmacological strategies to complement standard care. Among non-pharmacological options, dietary intervention represents a pragmatic adjunct to standard care, given its favourable safety profile, feasibility, potential cost-effectiveness, and high patient acceptability [10].

Plant-based diets are characterised by a predominance of plant-derived foods and a reduced intake of animal-derived foods, particularly red and processed meat [11]. Higher intakes of dietary fibre, polyphenols, and antioxidant nutrients have been proposed to modulate inflammatory signalling, oxidative stress, and intestinal barrier function, processes implicated in the development and persistence of CIGT [12, 13]. Studies have shown that higher adherence to healthful plant-based dietary patterns is associated with lower systemic inflammation, whereas unhealthful patterns show the opposite association [14]. Moreover, a randomised controlled trial reported that a vegetable-based diet with controlled fibre intake reduced the incidence of cancer treatment-related diarrhoea [15]. Nevertheless, despite evidence linking diet to inflammatory status and treatment-related gastrointestinal outcomes, robust evidence remains limited regarding whether plant-based dietary interventions can mitigate CIGT in patients with CRC during active chemotherapy.

### Explanation for the choice of comparator {9b}

The comparators were selected to reflect routine nutritional management during FOLFOX chemotherapy and to enable an interpretable assessment of the incremental effect of a plant-based dietary intervention. The conventional dietary intervention comparator represents standard supportive dietary guidance commonly provided in oncology care and therefore offers a clinically relevant benchmark. The comparator of conventional dietary intervention supplemented with an Oncology Complete Nutritional Formula was included because comprehensive oral nutritional formulas are frequently used when chemotherapy-related gastrointestinal symptoms compromise appetite or oral intake. Including this arm allows the trial to distinguish effects attributable to a structured plant-based dietary pattern from those related to nutritional supplementation alone.

## Objectives {10}

This trial aims to evaluate the efficacy and safety of a plant-based dietary intervention for mitigating CIGT in patients with CRC receiving FOLFOX chemotherapy, compared with a conventional dietary intervention and a conventional dietary intervention supplemented with an Oncology Complete Nutritional Formula.

Primary objective: To compare changes in gastrointestinal symptom burden, serum inflammatory biomarkers, and gut microbiota composition and structure from baseline to week 6 among the three study groups.

Secondary objectives: To compare, from baseline to week 6, dietary intake and diet quality, emotional status, fatigue, nutritional status, and laboratory measures (blood counts and serum nutritional, metabolic, immunological indicators, and tumour markers) across groups.

Safety objective: To assess safety by comparing intervention-related adverse events (including food allergy, hypoglycaemia, and unintended weight loss) across groups.

## Methods: patient and public involvement, and trial design

### Patient and public involvement {11}

Patients and the public were not involved in the design of the study, including the formulation of the research question, selection of outcomes, or development of the intervention and recruitment strategy. Patients and the public will not be involved in the conduct of the trial (e.g., data collection or study management). During the trial, participant feedback on the acceptability and feasibility of the dietary interventions will be collected to inform refinement of the intervention materials and implementation procedures. The study results will be disseminated to participants in a plain-language summary and, where appropriate, through institutional communication channels.

### Trial design {12}

The trial is designed with a superiority framework and an allocation ratio of 1:1:1. Participants will be randomised to receive a plant-based dietary intervention, a conventional dietary intervention, or a conventional dietary intervention supplemented with an Oncology Complete Nutritional Formula for a 6-week intervention period. The trial protocol is reported in accordance with the Standard Protocol Items: Recommendations for Interventional Trials (SPIRIT) guidelines [16]. The study flow is illustrated in Fig. 1.

**Fig. 1 Fig1:**
[figure not shown]
Flow diagram of the study design

## Methods: participants, interventions and outcomes

### Trial setting {13}

This study will be conducted in Chengdu, China, at two hospital sites: West China Fourth Hospital, Sichuan University, and The Seventh People’s Hospital of Chengdu. Participants will be recruited from the oncology departments of the participating hospitals, where FOLFOX chemotherapy is routinely delivered. The trial will be implemented across inpatient chemotherapy wards and affiliated outpatient services that provide standard supportive care for patients with CRC.

## Characteristics of the people who are needed for the trial

**Table Taba:** 

Characteristic	The people we would expect to see included
Age	Adults 18–65 years with CRC receiving FOLFOX; we expect most participants to be middle-aged/older adults within this range. Age will be recorded at baseline and summarised by group (mean [standard deviation] or median [IQR])
Sex	Both male and female participants are expected. Sex will be extracted from the medical record at baseline and reported by group (n, %)
Gender	Not applicable (sex recorded as male/female from medical records)
Race, ethnicity and ancestry	We expect the majority of participants to be Han Chinese, given the regional population structure and the hospitals’ catchment area; ethnic minority categories will be recorded if self-reported/available and reported descriptively by group
Socioeconomic status	No restrictions are applied. Given the setting (two tertiary hospitals), a broad range is expected. We will collect feasible socioeconomic status indicators (e.g., education level and health insurance type; optionally employment status) and report distributions by group
Geographic location	Recruitment is from two hospitals in Chengdu, Sichuan, China; therefore, most participants are expected to reside in Chengdu and surrounding areas, with a predominance of urban residents. Residence (city/county; urban/rural) will be recorded at baseline and reported by group, acknowledging limits to generalisability beyond this region
Other characteristics relevant to the trial	We anticipate variation in clinical features relevant to tolerability (e.g., disease stage, ostomy status, baseline nutritional risk). These will be collected from medical records and reported descriptively by group

### Eligibility criteria for participants {14a}

#### Inclusion criteria

Participants will be eligible if they meet all of the following criteria:Aged 18–65 years.Histologically confirmed CRC and scheduled to receive FOLFOX chemotherapy, with an anticipated total chemotherapy duration of ≥ 2 months.BMI 20–35 kg/m^2^ and KPS ≥ 60.Able to communicate effectively and complete study procedures and questionnaires.Able to consume an oral diet and not requiring enteral or parenteral nutrition support at baseline.Self-reported motivation to change dietary habits rated as “very motivated” or “motivated”.Willing to participate voluntarily and provide written informed consent.

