## Intervention and comparator

### Intervention and comparator description {15a}

This is a multicentre, stratified, randomised controlled trial comparing three different dietary interventions for CRC patients undergoing FOLFOX chemotherapy: plant-based dietary intervention, conventional diet, and oncology nutritional formula. Each group will receive a 6-week dietary intervention during their chemotherapy cycle.

To minimise non-specific (attention/support) effects across groups, the frequency and mode of participant contacts will be standardised across all three arms. All participants will receive: (i) a structured face-to-face education session at baseline during chemotherapy admission (T0), and (ii) daily remote follow-up throughout the 6-week intervention period (telephone/WeChat) delivered according to a prespecified checklist, primarily to record daily dietary intake and monitor symptoms/adverse events. Brief reinforcement will also be provided during inpatient chemotherapy visits when applicable. Unscheduled contacts for symptom management are permitted in all groups and will be documented. Daily contacts are primarily for data capture and safety monitoring; no additional individualized dietary counselling beyond the allocated programme will be provided unless clinically indicated.

The plant-based diet will be based on the latest evidence for nutritional and dietary interventions in managing CIGT. The diet will include fruits, vegetables, whole grains, nuts, and anti-inflammatory beverages such as green tea, soya milk, and peanut-legume juice. It will emphasize reducing red and processed meat intake and limit fish consumption. Participants will also be encouraged to follow the Dietary Guidelines for Chinese Residents [17], which include recommendations on fluid intake (1,500–1,700 ml/d), limited salt (< 5 g/d), and oil (25–30 g/d). Weekly food supplies, printed materials, and cooking videos focused on plant-based nutrition will be provided to support adherence. Quantitative targets (intervention “dose”) were prespecified to operationalize the plant-based dietary strategy: (i) vegetables and fruits ≥ 500 g/d; (ii) whole grains 70–90 g/d and legumes ≥ 1 serving/day on most days; and (iii) red and processed meat ≤ 500 g/week (fish, if consumed, limited to ≤ 300–450 g/week). These targets will be reinforced during follow-up and assessed using diet records and Food Frequency Questionnaire (FFQ)-based scoring.

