### Outcomes {16}

#### Primary outcomes

Grades of CIGT: CIGT will be assessed using the National Cancer Institute Common Terminology Criteria for Adverse Events (CTCAE) v5.0 [18]. Prespecified gastrointestinal toxicities include nausea, vomiting, anorexia, oral mucositis, and diarrhoea. Assessments will be conducted at baseline (T0), day 3 post-chemotherapy (T1), week 1 (T2), week 3 (T4), and week 5 (T6). The confirmatory clinical endpoint is the participant-level incidence of experiencing any prespecified CTCAE gastrointestinal toxicity of grade ≥ 2 during follow-up. Longitudinal CTCAE grades, time-specific binary indicators (grade ≥ 2 at each time point), and the maximum CTCAE grade across the prespecified toxicities will be analysed and reported as supportive outcomes (reported as n [%] and median [IQR]).Serum inflammatory biomarkers: Serum biomarkers, including interleukin-6 (IL-6) and C-reactive protein (CRP), will be measured at the following time points: T0 and week 6 post-chemotherapy (T7). Outcomes will be summarised as concentrations at each time point and change from baseline to week 6 [reported as mean ± standard deviation (SD)].Stool-based multi-omics: Stool samples will be collected at T0, T1, T2, T3, and T7 using a standardised kit and stored at − 80 °C until batch processing. Shotgun metagenomic sequencing will be performed to characterise taxonomic composition and metagenome-derived functional profiles [19]. Sequencing reads will undergo prespecified quality control, filtering, and taxonomic/functional profiling using validated pipelines. Untargeted stool metabolomics will be performed in parallel, with pooled quality control (QC) samples, process blanks, and internal standards included and run order randomised. Metabolomics data will be processed using prespecified procedures (peak detection, alignment, QC-based feature filtering, normalisation/transformation, and batch/drift correction), and metabolite annotation will be supported by tandem mass spectrometry (MS/MS) spectral matching against curated libraries. Feature-level and pathway-level analyses will control multiple testing using false discovery rate procedures. Outcomes will be summarised as within-sample diversity, between-sample dissimilarity, and longitudinal changes in the relative abundance/intensity of key taxa, functional features, and metabolite features/pathways (reported as change from T0 at each time point).

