### Participant timeline {18}

T0 is defined as baseline (before initiation of the allocated dietary intervention and within the chemotherapy admission). Follow-up time points are anchored to the start of the chemotherapy cycle: T1, day 3 post-chemotherapy; T2, week 1; T3, week 2; T4, week 3; T5, week 4; T6, week 5; and T7, week 6. There is no run-in or washout period. After eligibility screening and written informed consent, participants will be randomised (1:1:1) to one of three dietary strategies and followed for 6 weeks across inpatient chemotherapy and the home-based interval period. Assessments will be conducted in person during inpatient visits when feasible and otherwise via scheduled telephone/WeChat contacts according to the timetable below. Table 2 shows the participant timeline.

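### The abstract admits patients already on FOLFOX, but the duration criterion counts total rather than remaining treatment, so late-course entrants can qualify and be assessed off chemotherapy

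*Protocol article*

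**What the plan says.** The Inclusion criteria (Eligibility criteria for participants {14a}) require patients to be "scheduled to receive FOLFOX chemotherapy, with an anticipated total chemotherapy duration of" at least 2 months. This is the only criterion that bears on chemotherapy exposure during follow-up. The Exclusion criteria set no limit on prior cycles and no minimum remaining treatment.

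The abstract (Methods) describes the population as adults "receiving (or scheduled to receive) FOLFOX chemotherapy at two hospitals in Chengdu, China". The table of expected participants has, in its Age row, "Adults 18–65 years with CRC receiving FOLFOX".

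Intervention and comparator description {15a} says "Each group will receive a 6-week dietary intervention during their chemotherapy cycle". Participant timeline {18} places T0 "before initiation of the allocated dietary intervention and within the chemotherapy admission", and adds: "Follow-up time points are anchored to the start of the chemotherapy cycle". It does not say which cycle. Participants are "followed for 6 weeks across inpatient chemotherapy and the home-based interval period".

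Under Outcomes {16}, toxicity is graded at T0, day 3 (T1), week 1 (T2), week 3 (T4) and week 5 (T6). IL-6 and CRP have one post-baseline measurement, at week 6 (T7). The last stool sample is also at T7. Randomisation {21b} is stratified by site and sex only.

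**The concern.** The trial asks about gastrointestinal toxicity during FOLFOX over a 6-week window. The entry rule should therefore ensure that treatment is planned to continue through that window. A rule on total duration does so only when the course begins at T0. For a patient already on treatment, the relevant quantity is total duration minus time elapsed, and the criterion does not constrain it.

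The abstract says that such patients may enter. The inclusion criterion does not clearly exclude them either, because a patient in mid-course is also scheduled to receive the next cycle. Two sites could therefore apply the rule differently.

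A patient whose course ends shortly after T0 has fewer chances of a grade 2 or higher event in any arm, so the absolute difference between arms shrinks. That patient's only follow-up IL-6 and CRP values, and the week 6 stool sample, would be taken off chemotherapy.

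**Working it through.** **1. The plan's own figure.** Inputs from Sample size {19}: proportions 0.176 and 0.533, two-sided alpha 0.025, 80% power, 20% loss. With the unpooled two-proportion Z formula:

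n = (2.2414 + 0.8416)² × (0.176×0.824 + 0.533×0.467) / (0.533 − 0.176)² = 9.505 × 0.3939 / 0.12745 = 29.4, so 30 per group.

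30 / 0.8 = 37.5, so 38 per arm and 114 in total. The stated figures reproduce, and power at 30 per group is 80.9%. (The pooled-variance version needs 33 per group and gives 75.8% at 30.) The point does not rest on a sample-size error.

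**2. Timing.** Two months is about 8.7 weeks. Weeks remaining = total − weeks elapsed at T0.

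- Starting at T0: 8.7 weeks remain, which covers the 6 weeks.
- More than 8.7 − 6 = 2.7 weeks into a 2-month course: treatment ends before the week 6 samples.
- More than 8.7 − 5 = 3.7 weeks in: it ends before the week 5 grading.
- More than 8.7 − 3 = 5.7 weeks in: it ends before the week 3 grading.

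All of these patients satisfy a total of at least 2 months. With a longer course the same holds for its last weeks. T0 falls within a chemotherapy admission, so T1 and T2 follow chemotherapy for everyone. The assessments at risk are T4, T6 and T7.

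**3. Illustrative loss of power.** The documents give neither the share f of late entrants nor how risk is spread over the four follow-up gradings. Both are assumptions here. Suppose that a late entrant is at risk only at T1 and T2, and that those two gradings carry a fraction e of the cumulative hazard. The late entrant's risk is 1 − (1 − p)^e, and the arm's risk is the mixture (1 − f)p + f[1 − (1 − p)^e].

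- Equal risk at each grading (e = 0.5; per-visit risk 17.3% control, 4.7% diet): late-entrant risks are 31.7% and 9.2%, a difference of 22.4 points against the planned 35.7.
- T1 and T2 carry 70% of the hazard (e = 0.7): 41.3% and 12.7%, a difference of 28.6 points.

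Power = Φ(difference / √{[q₁(1−q₁) + q₂(1−q₂)]/30} − 2.2414), where q₁ and q₂ are the mixed risks:

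| Share f | Difference, e = 0.5 | Power, e = 0.5 | Difference, e = 0.7 | Power, e = 0.7 |
|---|---|---|---|---|
| 0 | 35.7 points | 81% | 35.7 points | 81% |
| 10% | 34.4 | 78% | 35.0 | 79.5% |
| 20% | 33.0 | 75% | 34.3 | 78% |
| 30% | 31.7 | 72% | 33.6 | 76% |
| 50% | 29.1 | 66% | 32.2 | 73% |

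As a rough guide to f, suppose that every patient entered at a random point of the course. The share within 3 weeks of its end would be 3/8.7 = 34% for the shortest permitted course and 3/26 = 12% for an assumed 26-week course. Any patients who enter at their first cycle lower both figures.

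**The case against.** The strongest reply is that the eligibility section governs, and that it looks forward: patients are scheduled, and the duration is anticipated. If that means not yet started, total and remaining duration coincide and the rule is adequate. This stands as far as it goes. A reader might infer that a total-duration rule is wrong in itself, but it fails only if patients already on treatment may enter. The abstract says they may, and the criterion's wording does not plainly rule them out.

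The table's Age row does not add a second contradiction. It describes the people expected in the trial and sets no entry rule, so it only needs aligning. Nor does the criterion's second use of the word chemotherapy open the door to other regimens, since the same sentence has just named FOLFOX.

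A reader might also infer bias. The documents do not support that: position in the course is fixed before randomisation, so it cannot systematically favour an arm. What remains is dilution, plus chance imbalance in a factor that is not stratified.

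The larger losses in the table are not established either. Power of 66% needs half of the participants to enter at the very end of their course and equal risk at all four gradings, and nothing in the protocol suggests such late entry. All the figures are also taken at 30 per group, that is, after the full 20% loss. With all 38 per arm evaluable, a 20% share under equal risk still leaves about 85%.

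**Conclusion.** The concern holds in a limited form. The abstract and the inclusion criterion disagree on whether patients already on FOLFOX may enter. On the abstract's reading, the only exposure criterion does not ensure treatment through follow-up, and nothing in the exclusions, the timeline or the stratification closes the gap.

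The consequence is a smaller observable difference and a modest loss of power: from 81% to between 75% and just under 80% for shares of 10 to 20%. This rests on an assumed share, on an assumed split of risk between early and late gradings, and on no event risk at weeks 3 and 5 for late entrants. Power at 30 evaluable per group is only just above the 80% target, so even a 10% share takes it slightly below. The point should be fixed, but it does not threaten the validity of the comparison. Confidence is moderate.

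**What to change.** Reconcile the abstract with the inclusion criterion on whether patients already receiving FOLFOX may enter, and align the descriptive wording in the table of expected participants. Replace the total-duration condition with one on planned FOLFOX remaining from T0 that covers the 6-week follow-up. This changes who is enrolled, not anyone's chemotherapy, and the planned 114 stands.

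Record the cycle number at T0 for every participant, including the 7 enrolled by 23 January 2026. Those 7 stay in the intention-to-treat analysis whether or not they would meet the revised wording.

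Adjustment for first versus later cycle is optional and can be left to the SAP; Statistical methods {27a} already allows further prespecified covariates. It is not free: at 30 per group, a two-arm comparison expects only about 30 × (0.176 + 0.533) = 21 events, already shared by the group, site and sex terms.

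The cost is a wording amendment, one chart item and a few late-course patients lost at screening. With 107 of 114 participants still to be recruited at that date, the change would reach nearly the whole trial if made promptly.
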